### Randomization

Couples are randomized by the researchers by means of flipping a coin. Conditions are predetermined (before registration of the couple) by this method for every block of ten couples, to exclude any kind of influence the researchers might have. The randomization is single-blind; couples do not know that there are two different conditions until the debriefing that is given after the follow-up questionnaire. When participants do not fill in the follow-up questionnaire, the debriefing is sent to them by e-mail.

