### Measures

Table 1 shows all variables that are measured (including exploratory/potential covariates).

**Table 1 Tab1:** Content of the baseline, diary and follow-up questionnaire

Measures	Baseline		Diary		Follow-up	
	*Smoker*	*Partner*	*Smoker*	*Partner*	*Smoker*	*Partner*
Baseline information						
Socio-demographics	X	X				
Smoking details and history	X	X			X	
Quit attempt history	X					
Primary & Secondary outcomes						
Number of cigarettes smoked	X		X	X	X	X
Hiding of smoking	X				X	
Duration of abstinence					X	X
Perceived frequency of smoking-related conflicts (SRC)	X	X			X	X
Relationship satisfaction	X	X	X	X	X	X
Smoking dependence	X		X	X	X	
Smoking now compared to before quit attempt					X	X
Mediators						
Details of partner contact			X	X		
Partner responses			X	X		
Partner responses to difficult moment			X	X		
Exploratory outcomes and potential covariates						
Attitude towards smoking	X	X				
Affect (PANAS)	X	X	X	X		
Opinion partner about quitting/smoking behaviour	X	X				X
Influence of SRC	X					
Perceived susceptibility	X	X			X	X
Perceived relatedness	X	X			X	X
Self-compassion towards relapse			X	X	X	X
Intention to quit	X				X	
Taking steps to go smoking			X			
Use of smoking replacement			X	X	X	X
Difficulty quitting			X	X		
Adherence to planning			X	X	X	X
Helpfulness of planning			X	X	X	X
Conflicts not related to smoking			X	X		
Interference of quitting with relationship			X	X		
Details social contacts			X	X		
Interference of quitting with social contact			X			
Other health behaviours	X	X				
SRC initiator	X	X				
SRC recentness	X	X				
SRC pattern	X	X				
Partner interaction questionnaire	X	X				
Details most difficult moment			X	X		
Distraction from smoking			X	X		
Motivation to remain quit			X			
Evaluation of diary			X	X	X	X
Self-efficacy to quit	X		X	X		
Daily activities			X	X		
Role of smoking in break-up					X	X
Influence of plan on relationship					X	X
Missing smoking					X	

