### Statistical analyses

For our primary aim we will compare the proportion of successful abstainers in both groups, weekly (day 7, 14, 21) and after 3 months (primary outcome variable). Primary analyses are conducted with baseline and follow-up data according to the intention-to-treat approach. Secondly, we will compare the number of cigarettes smoked between the groups, controlling for baseline smoking (secondary outcome variable). Similar comparisons will be made for relationship satisfaction (secondary outcome variable). Additional independent and paired post-hoc t-tests will be performed to examine between-group and within-group differences, and chi-square tests for categorical variables*.* For the secondary aim, we will examine the effects of partner interactions on same and next-day smoking behaviour and relationship satisfaction (concurrent and lagged effects). Multilevel modelling will be used to analyse the diary data [29]. The diary data is nested within individuals and couples. Multi-level analyses will take into account between-person variation (individual variation from the grand mean) as well as within-person variation (an individual’s daily variation from their personal mean). To examine the indirect effect of the intervention on smoking and relationship satisfaction via partner interactions, we will conduct a within-person mediation analysis, allowing for random intercepts and slopes [29]. We will check whether the randomization was successful regarding demographical, smoking and relationship variables. If not, those variables will be taken into account as covariates in the analyses. 

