### Power analysis

In literature, 15.48% of the participants successfully quit smoking after an intervention using implementation intentions, measured one month later [3]. Therefore, we expect an abstinence rate of 15% in the individual planning (control) group. With a power of 0.8 and an alpha of .05, we need 70 couples per group to detect a relevant increase in effectiveness of 20% (primary aim). Additionally, we consider a minimal decrease of 50% in number of cigarettes, between baseline and follow-up, relevant [30].

A minimum sample of 50 cases is advised in a multi-level design [31] and diary studies in this research area are usually between 60 and 100 participants. Considering a power of .80 and an alpha of .05, the power analysis showed that a net sample size of 82 couples is sufficient to find an effect size of at least .3 (a medium effect) in the diary between smoking-related interactions and smoking behaviour (secondary aim). Therefore, with the sample of 140 couples we have sufficient power to detect a relevant difference in effectiveness of the intervention as well as the research questions related to the diary data. To take into account drop-out, we aim to include 15% extra couples.

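### For the primary abstinence comparison, covariates are chosen by observed baseline imbalance, so the primary model is not fixed in advance and usually omits plausible prognostic variables

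*Protocol article*

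**What the plan says.** The Statistical analyses section sets the primary comparison as follows: "we will compare the proportion of successful abstainers in both groups, weekly (day 7, 14, 21) and after 3 months (primary outcome variable". No covariate is attached to it.

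The section closes with the covariate rule: "We will check whether the randomization was successful regarding demographical, smoking and relationship variables", and then "If not, those variables will be taken into account as covariates in the analyses". It gives no criterion for failing the check and no closed list of variables, only three broad classes.

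One secondary outcome is treated differently. For cigarettes smoked, "we will compare the number of cigarettes smoked between the groups, controlling for baseline smoking (secondary outcome variable", whatever the balance. The next sentence promises comparable analyses for relationship satisfaction.

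The Measures section says "Table 1 shows all variables that are measured (including exploratory/potential covariates". In Table 1 the smoker's baseline questionnaire includes number of cigarettes, smoking dependence, quit attempt history and self-efficacy to quit. The Randomization section says "Couples are randomized by the researchers by means of flipping a coin", with conditions set in advance for each block of ten couples.

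**The concern.** Conditions are assigned by coin flip before a couple registers, so any baseline difference between the groups is a chance event. Finding one does not show that randomisation failed, and finding none does not show that it succeeded. What improves an adjusted comparison is a covariate's relation to the outcome, and the rule does not look at that. An irrelevant variable enters when it happens to differ. A strongly prognostic one stays out when it happens to look balanced, which is the usual case.

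Two things are at stake. First, the model behind the primary result is settled only after the baseline data have been inspected, by a criterion the article does not define. Second, precision that could be gained from data already collected is mostly given up. The plan is also uneven: it fixes a baseline covariate for a secondary smoking outcome but none for the primary one.

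**Working it through.** **Inputs from the Power analysis section.** For control abstinence, "we expect an abstinence rate of 15% in the individual planning (control) group". The target is "to detect a relevant increase in effectiveness of 20% (primary aim", read here as percentage points, so 15% versus 35%. Power is 0.80 and alpha .05 (taken as two-sided), with 70 couples per group.

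**Step 1: reproduce the plan's figure.** Two proportions, unpooled variance:

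n = (1.960 + 0.842)² × [0.15×0.85 + 0.35×0.65] / 0.20² = 7.849 × 0.355 / 0.04 = 69.7, rounded up to 70 per group.

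This matches. It is an unadjusted calculation. The pooled-variance formula gives 73 per group, and power at 70 per group is then 78.6%. The sample size does not need to change for this point.

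**Step 2: how often would the check flag something?** Assumptions, none stated in the article: each variable is tested at p < .05, the variables are independent, and k of them are checked. The chance of at least one flag is 1 − 0.95^k, and the expected number of flags is 0.05k.

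| k | At least one flag | Expected flags |
|---|---|---|
| 10 | 40% | 0.5 |
| 15 | 54% | 0.75 |
| 20 | 64% | 1.0 |

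Any one variable is flagged about 5% of the time, so a given predictor is left out about 95% of the time, however strong it is.

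**Step 3: what does the rule cost?** Simulation with 70 per arm, marginal abstinence of 15% and 35% (15% in both arms under the null), one standard-normal baseline predictor, logistic Wald test and 6,000 runs per scenario. The rule adjusts only if a baseline t-test gives p < .05. The predictor strengths are assumed.

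| | Odds ratio 1.65 per SD | Odds ratio 2.72 per SD |
|---|---|---|
| Power, unadjusted | 78.1% | 78.7% |
| Power, imbalance rule | 78.3% | 79.2% |
| Power, always adjusted | 79.9% | 84.4% |
| Type I error, imbalance rule | 4.1% | 3.8% |
| Type I error, always adjusted | 4.3% | 4.4% |

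The loss against always adjusting is 79.9 − 78.3 = 1.6 points at the weaker strength and 84.4 − 79.2 = 5.2 points at the stronger. A second simulation of 2,000 runs, with ten variables checked and an odds ratio of 2.7 per SD, agrees: 77.7% unadjusted, 77.6% under the rule and 83.5% with the predictor prespecified, with type I error about 5% throughout. In power terms the rule behaves almost like no adjustment.

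**Step 4: events available.** 70 × 0.15 + 70 × 0.35 = 10.5 + 24.5 = 35 expected abstainers.

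**The case against.** The article says only that balance will be checked. It names no test, threshold or number of variables, and a condensed article may leave those to a fuller plan. That stands as far as the size goes: the probabilities in step 2 and the power figures in step 3 rest on assumptions. It does not remove the point, because the trigger itself, adjustment conditional on observed imbalance, is stated outright.

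Nothing is lost relative to the stated sample size, which is for an unadjusted comparison. This is also true. The loss is measured against what the collected baseline data could offer. An unadjusted comparison fixed in advance would be a legitimate primary analysis and would end the data dependence, but it would forgo the gain in power.

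Four stronger readings are tempting, and none is supported:

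- A reader might infer that covariates enter the whole plan only through imbalance. Number of cigarettes is adjusted for baseline smoking regardless, and relationship satisfaction plausibly is adjusted in the same way.
- A reader might infer that known predictors of quitting are left out. The article gives no variable that label. Table 1 shows only that plausible ones are measured.
- A reader might infer that false positives are inflated. The simulations show no such inflation.
- A reader might infer that the rule overloads a logistic model with 35 events. On the assumptions of step 2 it adds 0.5 to 1 covariate on average, and three or more with probability of about 1% (k = 10) to 8% (k = 20). The fix below always adds two.

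**Conclusion.** The point holds for the abstinence comparison and should be corrected, although it does not threaten the validity of the test. The rule lets chance and an undefined criterion decide which primary model is fitted, and it usually leaves out baseline variables that could plausibly sharpen the estimate.

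The power cost ranges from near-trivial to modest, about 1.6 to 5 points. It depends on assumed predictor strengths of 1.65 to 2.72 per SD and on reading the check as a 5% test. The 40% to 64% chance of at least one flag further assumes 10 to 20 independent variables; correlated variables would change it. The case for prespecification does not depend on these figures, since a trigger based on imbalance is the wrong basis for choosing covariates at any threshold.

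**What to change.** - Delete the imbalance trigger.
- Name a short covariate list for the abstinence model, to be used whatever the balance. Baseline cigarettes per day and baseline smoking dependence are one reasonable choice. Quit attempt history and self-efficacy are also measured at baseline, and the choice is for the investigators to make and fix in advance.
- Report a standardised risk difference from that model, so that the planned comparison of proportions is kept.
- Present baseline characteristics descriptively, and do not use them to judge whether randomisation worked.
- For relationship satisfaction, only confirm that the comparison is adjusted for the baseline score of the same scale.

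The change is to wording; it needs no new data and no larger sample. There are two downsides. The adjusted odds ratio is conditional on the covariates and so differs in meaning from the unadjusted one, which is why the standardised risk difference should stand beside it. And two covariates plus condition make three coefficients on about 35 expected events, or 35 / 3 ≈ 12 events each, so the list should stay short.

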### Power analysis

In literature, 15.48% of the participants successfully quit smoking after an intervention using implementation intentions, measured one month later [3]. Therefore, we expect an abstinence rate of 15% in the individual planning (control) group. With a power of 0.8 and an alpha of .05, we need 70 couples per group to detect a relevant increase in effectiveness of 20% (primary aim). Additionally, we consider a minimal decrease of 50% in number of cigarettes, between baseline and follow-up, relevant [30].

A minimum sample of 50 cases is advised in a multi-level design [31] and diary studies in this research area are usually between 60 and 100 participants. Considering a power of .80 and an alpha of .05, the power analysis showed that a net sample size of 82 couples is sufficient to find an effect size of at least .3 (a medium effect) in the diary between smoking-related interactions and smoking behaviour (secondary aim). Therefore, with the sample of 140 couples we have sufficient power to detect a relevant difference in effectiveness of the intervention as well as the research questions related to the diary data. To take into account drop-out, we aim to include 15% extra couples.

## Discussion

Our study is the first to examine the immediate effectiveness and effectiveness over time, of dyadic planning to quit smoking in single-smoking couples. Current research on dyadic planning is limited and shows mixed results. Previous RCTs mainly focused on the implementation of new behaviours (e.g., increasing activity or doing pelvic-floor exercises). This RCT will give more insight into the effectiveness of dyadic planning when it is used to quit an unhealthy behaviour. If cooperating with a non-smoking partner improves the planning intervention, it can be considered as a valuable and low-cost addition to existing smoking cessation interventions.

Partner interactions play an important role in a quit attempt [14, 15, 32]. Therefore, in addition to examining the effectiveness of the planning intervention, we will examine daily partner interactions that might be the working mechanism behind a successful couple intervention. The experience sampling method is an ideal way to examine partner support and its daily effects and fluctuations. An end-of-day diary could show fluctuations in partner support over the course of a quit attempt, the effect that support has on smoking behaviour, and whether couples show differences in support that might be affected by whether their planning was dyadic or individually. For example, it could show differences between the intervention and control group in how the partner responds to difficult moments. If certain partner interactions are found to have a positive influence on the abstinence rate, these could be advised in cessation interventions in which a non-smoking partner is involved. One could instruct partners how to provide support in general and during difficult moments.

As we also measure relationship satisfaction on a daily basis, we are able to see associations between daily interactions in general and related to the quit attempt and how these are associated with relationship satisfaction. Results could show a trade-off; some behaviours might be helpful for the quit attempt, but damaging to the relationship. Therefore, the results of this study can be used not only to provide a better cessation intervention, but also to help maintain a good relationship satisfaction during the difficult time of a quit attempt.

### Strengths and limitations

Strengths of the study include the combination of a promising and low-cost quitting smoking intervention with the experience sampling method. The experience sampling method is the ideal way to examine daily effects and fluctuations in smoking and partner behaviours, which might explain and contribute to the effectiveness of the intervention. Limitations are that we solely rely on self-report and have no no-planning control group. Nevertheless, a meta-analysis showed that self-reports of smoking are accurate in most studies [33]. Ideally, a third group should be added to this study, in which the smoker quits without a planning intervention. However, due to the effect of implementation intentions already found in literature [3, 5], the focus of this study is on examining the effect of the dyadic process. A third group would require a larger sample size, thereby jeopardizing the feasibility of the study.

## Conclusion

This study will provide more insight into whether involving a non-smoking partner could improve planning interventions, and whether and which partner interactions underlie this effectiveness. When proven effective, this planning intervention in combination with coaching for the non-smoking partner will be a valuable and low-cost addition to existing smoking interventions.
